**Text Message Procedures**

Participants may receive text messages throughout their time in the study. Text messages will be sent either via Televox or Google Voice. Any messages containing sensitive information, such as patient health information, will be sent using Televox, as it is HIPAA compliant and secure. No messages will be sent without first receiving participant consent. Consent to receive text messages will be documented in the participant’s study file. Text messages may include communications about recruitment, scheduling, visit reminders, survey compliance updates, abstinence confirmation, and safety check ins.

**Termination of Participation**

Participants will be terminated from this study if they fail to comply with study procedures or if in the opinion of the principal investigator, can no longer safely participate.

1. **Risks and Discomforts**

**Potential risks in the study are considered minimal and include:** Psychosocial, Social and Legal Risks: There are no uncommon psychological, social, or legal risks associated with participation in this study. Periods of voluntary cannabis abstinence are not uncommon for adolescent users as they often take breaks for participation in sports, family vacations, etc. There is a slight risk that the questionnaires and interviews may contribute to temporary discomfort when participants are asked about distressing symptoms (e.g., suicidal thoughts). Notably, prior research has shown that answering questions about suicidal thoughts and actions does not increase psychological distress or increase one’s suicidal thoughts/behaviors (Reynolds et al., 2006). Nevertheless, a study staff member will monitor the EMA responses and in the event of significantly worsening depressive symptoms, suicidal thoughts, or behaviors (described in detail below), will alert a clinically trained staff member who will follow-up within 24 hours. A doctoral level clinician, including PI [name], will be on call should they be needed.

**Fitbit Risks:** Fitbits used for sleep and activity data pose minimal risk and do not alter the current level of risk for the main study. A small portion of people either find the device uncomfortable or have reactions to the device or band. Alternate material Fitbit bands will be ordered as needed.

**Confidentiality and Privacy**: Another potential risk to participants is breach of confidentiality. However, protecting the confidentiality and integrity of our research participants is a top priority for this MGH project, and the risk of loss of privacy is judged to be minimal. Data will be collected using REDCap (Research Electronic Data Capture; http://rc.partners.org/edcredcap) tools (Harris 2009) hosted with Partners HealthCare. Assessments will be administered via REDCap and smartphone EMA. REDCap, REDCap Survey systems, and smartphone EMA provide secure, HIPAA compliant, web-based applications. Confidentiality will be maintained by numerically coding all data and by keeping all data in password protected databases. In addition, this study will maintain a Certificate of Confidentiality from the National Institutes of Health. Some participants may be concerned that participating in this protocol will disclose their substance-using habits, particularly to school personnel and/or parents. During the telephone screener, if a participant is determined eligible and would like to be enrolled, we will make sure to tell participants that no information shared with study staff will be disclosed unless there are imminent safety concerns. We have taken several precautions, including masking language in the consent form, to reduce the likelihood that a participant’s parents/guardians will deduce that their child uses cannabis and has symptoms of depression. However, it is impossible to remove all risk that parents/guardians may deduce that their child uses cannabis and has symptoms of depression because we are only recruiting cannabis users who report depressive symptoms. During the telephone screener, we will make sure participants are aware of this and give them the opportunity to decline participation before any contact is made with parents. Additionally, both participants and parents/guardians will be made aware that no details disclosed during the study, including those relevant to use or mental health or substance use history, will be shared with the parents/guardians unless there is an immediate concern for safety.

There is a potential that we may need to break confidentiality for the proposed study. During the informed consent process, we will inform participants that all information they provide as part of the study is confidential, however, there is a risk that we will break confidentiality if the participant is at serious risk of harm to self. Our plan for risk monitoring and breaking of confidentiality adheres to guidelines set forth by a previously approved IRB protocol (#2015P000598) and a recent consensus statement from experts in the field of suicide and EMA, carefully considering participant safety without introduction of potentially iatrogenic effects involving reactivity to contingent risk assessment in EMA (Nock et al., 2021). Specifically, if a participant indicates serious risk of suicide (i.e., if they rate their intention of acting on their suicidal thoughts as 80 or more out of 100 on the EMA prompt), the EMA program will automatically prompt the participant again 15 minutes later. If the second prompt is not completed or if symptoms to not dissipate below 80/100, then a safety check-in by a clinically trained staff member will be initiated within 24 hours either by text (Televox; a HIPPA complaint, MGB-approved texting platform) or phone call. If a safety check in is initiated with the participant, parents/guardians will also be notified. We will have dedicated study staff for twice daily monitoring of daily EMA data 7 days a week for risk determinations. Phone-based risk assessments will only be conducted by a clinically trained staff member with a doctoral level clinician on standby.

If a participant rates their intention of acting on their suicidal thoughts as a 50 out of 100 or higher, the smartphone EMA application will send a push notification to the participant’s smartphone stating that (1) app data is not monitored in real time and (2) the participant should contact a member of their treatment team, call the suicide [contact]), or go to the nearest emergency room if they need additional help. This will ensure that participants at elevated but not imminent risk will still have access to suicide risk reduction resources. At the baseline visit, we will personalize a safety plan that will be programmed into the EMA application and “pushed” to the participant if he/she rates his/her intention of acting on suicidal thoughts as a 50 out of 100 or higher.

Parents and participants will be made clear of our risk monitoring protocol and plans for breaking confidentiality at the point of consent and throughout the protocol as necessary.

1. **Benefits**

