SI are temporarily relieved and stabilized through acute cannabis use (i.e., negative reinforcement).

*Hypothesis 1.1:* Negative mood will predict subsequent same-day cannabis use events as well as greater self-reported motivation to use cannabis for mood improvement (EMA Phase 1; Baseline as Usual).

*Hypothesis 1.2:* Negative mood and SI reported within one hour following cannabis use will be lower in intensity and less variable than mood and SI reported during same-day random-prompt EMA reports occurring ≥1 hours since last cannabis use (EMA Phase 1; Baseline as Usual).

*Hypothesis 1.3 (exploratory):* There will be within-subject correlates (e.g., concurrent other substance use, social context of use) and between-subject factors (e.g., cannabis use and depression severity, history of suicidal behavior) that moderate relationships between acute cannabis use and mood and SI.

**Aim 2:** To test if negative mood and SI decrease in overall (mean) levels and variability after cannabis

wash-out.

*Hypothesis 2.1:* Among CB-Abst but not CB-Mon, negative mood and SI reported during random prompt EMA reports will intensify and become more variable throughout the first week of sustained cannabis withdrawal (EMA Phase 2; Randomized Withdrawal) compared to random, non-use events during baseline cannabis use as usual (EMA Phase 1; Baseline as Usual).

*Hypothesis 2.2:* Negative mood and SI reported during EMA random prompts after 8 weeks of abstinence (EMA Phase 3; Randomized Sustained Abstinence) will be lower in intensity and variability than negative mood and SI reported during EMA random prompts occurring during random, non-use events during baseline cannabis use as usual (EMA Phase 1; Baseline as Usual) and withdrawal (EMA phase 2; Randomized Withdrawal). There will be no difference in mood or SI intensity or variability across the 3 EMA phases in CB-Mon.

1. **General Description of Study Design**

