**Potential Benefits to Society**

Information developed from this study may help researchers in the future. The expected scientific yield of the project is substantial. There is much to be learned from the project. Findings have the potential to have measurable implications on policy, prevention, and treatment efforts. The greatest benefit will be to future cohorts of adolescents who will benefit from what is learned from this research project.

The risks associated with this study are minimal and reasonable, particularly in light of the fact that significant knowledge will be gained.

1. **Statistical Analysis**

**Data preparation.** Six negative affect measures will be defined via composite averages and individual scores using EMA items: 1) the average over 5 items assessing depleted mood (scores for feeling Sad, Self-hatred, Numb, Hopeless, and Fatigued), 2) the average over 2 items assessing negative cognitive impacts (scores for feeling Disinterested and Inattentive), 3) the average over 3 items assessing negative activation (scores for feeling Agitated, Irritated, and Anxious), 4) the average over 3 items assessing passive suicidal ideation (scores for Thoughts about death, Wishing suffering could be over, and Better off as dead), 5) the individual item for suicidal urges, and 6) the individual item for non-suicidal self-injury urges. All items will be measured on a 0 (No, not at all) – 100 (Yes, very much) scale. Acute cannabis use will be defined as a binary indicator variable (1 = self-reported use in the hour preceding the current random prompt, 0 = no use in the last hour).Additionally, whether cannabis was used in the last hour to improve negative mood will be assessed on a 0 (No cannabis use) and 1 (No, not at all) – 100 (Yes, very much) scale.

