**Data analysis.**

**Aim 1: To test if negative mood and SI are temporarily relieved and stabilized through acute cannabis use (i.e., negative reinforcement cycle).** We will only use phase 1 data, the 2-week baseline period in which all participants may use cannabis. *Hypothesis 1.1:* We hypothesize that negative affect measures for a) the current random prompt, and b) the prior random prompt (a lag-1 term) will predict 1) greater cannabis use independent of motivating reason (i.e., lower probability for the zero component of the model), and 2) higher scores for motivated cannabis use to improve negative mood. Negative affect measures will therefore be converted to z-scores for this analysis and included as predictors for both the zero and non-zero components of the model. *Hypothesis 1.2:* We hypothesize that the binary indicator for cannabis use in the last hour will predict lower, less variable scores for the negative affect measures. Therefore, the binary use indicator will be included as a predictor for the beta regression residual variance term as well. *Hypothesis 1.3 (exploratory):* There will be within-subject correlates (e.g., concurrent other substance use, social context of use) and between-subject factors (e.g., cannabis use and depression severity, history of suicidal behavior) that moderate relationships between acute cannabis use and negative affect.

**Aim 2: To test if negative mood and SI initially increase with the start of abstinence and then decrease in both mean levels and variability after cannabis wash-out.** We will use phase 1 – 3 data, including predictors for a) group differences (CB-Abst vs. CB-Mon), b) differences by phase (phase 3 vs. phase 1 and phase 2 vs. phase 1), and c) terms for the group by phase interactions. All terms will be included as predictors for the beta regression residual variance term as well. We will only include data for the CB-Abst group with confirmed abstinence for phases 2 – 3. *Hypothesis 2.1:* We hypothesize that CB-Abst will show higher mean negative affect scores and greater variability during phase 2 compared to phase 1, while CB-Mon will show no differences between phases. *Hypothesis 2.2:* We hypothesize that CB-Abst will show lower mean negative affect scores and less variability during phase 3 compared to phase 1, while CB-Mon will show no differences between phases.

**Exploratory analyses:** To further assess heterogeneity in suicidal ideation, we will conduct a set of

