**Planned Safety Monitoring**

This study will be monitored by PI, [name], using a Data and Safety Monitoring Plan (DSMP). It is considered necessary for the purpose of monitoring the safety of the study that PI review not only AEs and SAEs, but other data that may reflect differences in safety between treatment groups. This includes treatment retention rates, reasons for drop-out, and clinical outcomes. The main purposes of the DSMP will be to (1) ensure the continued safety of study participants, (2) monitor enrollment and retention, (3) confirm that there are no issues with data confidentiality, and (4) determine whether there is an unacceptable level of risk and increase number of adverse events due to cannabis abstinence. The PI will have overall responsibility for safety and data monitoring on a day-to-day basis.

An independent Data and Safety Monitoring Board (DSMB) will be appointed for this study to assess safety of this clinical trial by determining whether there is an unacceptable level of risk due to cannabis abstinence and whether an increased number of adverse events occur in the CB-Abst group compared with the CB-Mon group. A DSMB will be created at the beginning of year 1, as an independent body charged with ensuring that the safety of study subjects is protected and that the scientific goals of the study are being met. The DSMB will consist of four members whose expertise spans fields such as (1) digital monitoring via smartphones, (2) longitudinal research with high-risk suicidal participants, (3) adolescents, and (4) biostatistics. Each member of the DSMB will not otherwise be associated with the trial and the study investigators will not be members of the DSMB. Safety data will be reviewed by the DSMB every 6 months after the recruitment period begins. The DSMB will receive summary reports on recruitment, retention and description of all adverse events and review them at each biannual DSMB meeting. Subject information provided to the board will be identified only with study IDs to protect the confidentiality of subjects.

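### The risk section does not name the short-term worsening of mood and suicidal ideation that Hypothesis 2.1 predicts under assigned abstinence

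*Protocol*

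**What the plan says.** Under Risks and Discomforts the protocol opens with "Potential risks in the study are considered minimal and include" and continues "There are no uncommon psychological, social, or legal risks associated with participation in this study". Its only remark on abstinence follows: "Periods of voluntary cannabis abstinence are not uncommon for adolescent users as they often take breaks for participation in sports, family vacations, etc". The one psychological risk it names comes from the assessments: "There is a slight risk that the questionnaires and interviews may contribute to temporary discomfort when participants are asked about distressing symptoms". The other risks described are the Fitbit band and breach of confidentiality. The rating is repeated under Potential Benefits to Society: "The risks associated with this study are minimal and reasonable".

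The scientific sections say something different about abstinence. Hypothesis 2.1, under Specific Aims and Objectives, predicts for CB-Abst but not for the monitoring arm (CB-Mon) that "negative mood and SI reported during random prompt EMA reports will intensify and become more variable throughout the first week of sustained cannabis withdrawal". The Data analysis section restates Aim 2 as "To test if negative mood and SI initially increase with the start of abstinence", followed by a fall. Under Planned Safety Monitoring, one purpose of the safety plan is to "determine whether there is an unacceptable level of risk and increase number of adverse events due to cannabis abstinence", and an independent board receives a similar remit, comparing the two arms.

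**The concern.** The randomised intervention is abstinence, and the protocol predicts that its first week will raise scores for negative mood and suicidal ideation. A reader of the risk section alone would learn that answering questions may be uncomfortable, but not that the assignment itself may make mood or suicidal thoughts worse for a time.

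This matters because the population is aged 12 to 18, uses cannabis on most days and has current depressive symptoms. The risk section is the protocol's own account of what participants are exposed to, and it is a natural source for the consent texts and for ethics review. If it omits the predicted effect, documents drawn from it may omit it too.

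**Working it through.** No arithmetic applies: the point depends on no sample size, power or event figure. The check sets the sections side by side.

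1. **What is predicted, and for whom.** Hypothesis 2.1 concerns CB-Abst in week 1 after randomisation. Allocation is 1:1 with 100 planned per arm (Treatment Assignment and/or Randomization), so the prediction covers 100 of 200 participants, or half.

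2. **Whether the prediction includes suicidality.** Data preparation defines six negative affect measures, each analysed separately. Three of the six are passive suicidal ideation, suicidal urges and urges to non-suicidal self-injury. Hypothesis 2.1 also names suicidal ideation directly, so the prediction is not confined to general low mood.

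3. **Whether the protocol treats this as a possible harm.** It does. Planned Safety Monitoring asks both the safety plan and the independent board to judge risk due to abstinence. The Cannabis Withdrawal Scale is given at every visit from baseline to visit 12. The General Description of Study Design recognises withdrawal as a phase that generally subsides within four weeks.

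4. **Whether the risk section names it.** It does not. Nothing from Risks and Discomforts through the Benefits section attributes worsening of mood or suicidal ideation to withdrawal or to assigned abstinence. Worsening is mentioned only as something that staff will watch for in the EMA responses.

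5. **Whether the remark on voluntary breaks fills the gap.** It fits this trial poorly. Abstinence here is randomly assigned, lasts eight weeks and is paid for through contingency management. Eligibility requires no immediate plan to stop using cannabis in the next three months. The Baseline Visit section gives a family vacation as an example of a major departure from typical use, whereas the risk section cites family vacations as an occasion for ordinary breaks.

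Steps 1 to 3 show an effect that is hypothesised, measured and monitored. Steps 4 and 5 show that the risk section neither names it nor addresses it indirectly.

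**The case against.** The strongest reply has four parts.

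- **A hypothesis is not an established risk.** A directional prediction about mean EMA scores does not show that harm will occur, and a board asked to determine whether risk is unacceptable presupposes uncertainty. The sentence on psychological risks also says only that none are uncommon, not that there are none. This stands as far as it goes: the two sets of statements are not strictly incompatible. But a risk need not be certain to be foreseeable, and the monitoring section already treats this one as foreseeable.

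- **Worsening is watched for.** This stands. The risk section provides for clinical follow-up within 24 hours of significant worsening. Confidentiality and Privacy adds EMA review twice daily, seven days a week, automatic re-prompting, a personalised safety plan and notification of parents when a safety check-in is started. Visits on days 16, 19 and 21, in the week after randomisation on day 14, include the C-SSRS, the PHQ-9 and the withdrawal scale. These are safeguards, but they do not tell the reader that assigned abstinence may be a cause.

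- **Later benefit is expected.** This stands. Hypothesis 2.2 predicts lower and less variable scores in phase 3 than in phase 1, and the Aim 2 statement under Specific Aims mentions only the decrease. Expected benefit may justify an early risk, but it does not remove it.

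- **The rating of minimal risk is a judgement for the ethics committee.** This stands too. The point here is that the rating is given without reference to the predicted worsening.

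Three stronger readings are tempting, and the documents do not support them. A reader might infer that families are not told of this risk. The consent texts were not available for this review, and the consent procedures say that the consent form will set out the study and its associated risks and benefits. The masking language in that form is described as protecting against parents deducing cannabis use and depressive symptoms, not as hiding effects of abstinence. A reader might also take the d of 0.2 in the power analysis as the size of the expected harm. It is a power input that the protocol calls weak, and the pilot range of 0.19 to 0.44 is not tied to Hypothesis 2.1 or to any suicidality measure. Finally, a reader might infer that early worsening would be misclassified for adverse event reporting. The reporting section does use unexpectedness as a criterion, but it does not tie that to the risk section.

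**Conclusion.** The concern holds as an omission in the risk statement. Risks and Discomforts, and the sentence that repeats the rating under Potential Benefits to Society, do not name the temporary worsening of negative mood and suicidal ideation that the protocol predicts for week 1 of assigned abstinence and monitors as a possible risk. It bears on the 100 participants planned for CB-Abst. The protocol gives no expected size for the worsening, and none is claimed here.

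The gap is in naming the risk and attributing it to the assignment; there is no absence of safeguards. No endpoint, estimate or analysis changes. The conclusion rests on the protocol text alone and assumes nothing about the content of the consent documents.

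**What to change.** Reconcile Risks and Discomforts and Potential Benefits to Society with Hypothesis 2.1, the Data analysis text for Aim 2, and Planned Safety Monitoring:

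- List possible temporary worsening of mood and suicidal thoughts after stopping cannabis as a foreseeable risk of assignment to CB-Abst, with a cross-reference to the monitoring already described.
- State why the overall risk rating is still considered appropriate with that risk named. Whether it is appropriate remains for the ethics committee.
- Check that the parent consent, adolescent assent and adult consent texts say the same, and amend them if they do not.

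The cost is a wording amendment with ethics review, and possibly slightly lower enrolment.
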